### Intervention phase

Four weeks prior to the intervention phase, an investigator or designate will deliver intensive education targeting clinician knowledge, attitudes, and behaviors regarding the new oral care intervention to ICU cluster leads using a train-the-trainer model [28]. Cluster leads will comprise an ICU physician-nurse (or physician-pharmacist) dyad supported by unit-level oral care nurse champions. We will utilize an integrated knowledge translation (iKT) approach to facilitate practice change, including an iKT oral care tool kit supporting our oral care intervention [29] comprising a detailed oral care protocol (Table 1), touchpoint video (an edited video of ICU patient experiences and recommendations for oral care), and expert video instruction on oral care delivery (Additional file 1). To minimize bias, cluster leads will distribute the iKT oral care tool kit to frontline ICU nursing and allied health staff 2 weeks prior to the intervention phase.

**Table 1 Tab1:** Oral care bundle

Comprehensive oral care Q12 hours	Equipment	Procedure
1. Oral assessment	•Flashlight •Tongue depressor •Gloves •Face shield	•Explain procedure to patient •Gently open mouth or use mouth prop •Inquire about mouth/throat pain (0–10 NRS) •Use CPOT tool to evaluate pain in non-verbal pt. •Treat pain prior to proceeding
2. Tooth brushing	•Yankauer •12 or 14 French flexible catheter •Small soft-bristle or suction toothbrush •Sponge swabs •Sterile water •Gloves •Face shield	•Explain procedure to patient •Perform hand hygiene •Elevate HOB 30–45 degrees as tolerated •Use oral prop to open mouth as needed •Oral suction with Yankauer or sterile flexible catheter to remove secretions that may migrate down airway •Moisten toothbrush with sterile water •Connect suction toothbrush to continuous suction if applicable •Brush accessible teeth and gums for 2 full minutes or 30 s per quadrant; brush in one continuous line LUQ > RUQ > RLQ > LLQ •Gently brush tongue
3. Mouth and lip moisturizer	•Swabs •Mouth moisturizer/saliva replacement or sterile water •Gloves •Face shield	•Explain procedure to patient •Use oral prop to open mouth as needed •Use 1–3 swabs to apply moisturizer to oral mucosa, tongue, and lips
4. Deep oral suctioning	•Yankauer or flexible catheter •Gloves •Face shield	•Explain procedure to patient •Use oral prop to open mouth as needed •Deep oropharyngeal suction (above the cuff) to remove pooled secretions
Maintenance oral care Q4 hours and PRN	Equipment	Procedure
Mouth and lip moisturizer	•As above	•As above
Oral secretion removal	•As above	•As above

*CPOT* Critical-Care Pain Observational Tool, *HOB* head of bed, *PRN* pro re nata or “as needed”

The following oral care interventions will commence in the intervention phase for each step and become standard of care:
Intervention 1 (oral chlorhexidine de-adoption): Each cluster will de-adopt oral chlorhexidine from routine practice for all invasively ventilated patients. Use of routine oral chlorhexidine will not be permitted during the intervention period with the exception of patients prescribed chlorhexidine for non-standard care.Intervention 2 (oral care protocol): This two-part, nurse-led intervention incorporates comprehensive and maintenance oral care activities. Comprehensive care involves twice daily (morning and evening) a) oral assessment (inspection of the oral space, teeth and gums); b) tooth brushing; c) oral/lip moisturization; and d) suctioning oropharyngeal secretions above the cuff. Maintenance care involves, at a minimum of every 4 h and as needed, a) oral/lip moisturization; and b) suctioning oropharyngeal secretions above the cuff (Table 1).

One month after allocation to the intervention, a trained assessor will begin to observe fidelity of delivery of the oral care protocol and assess patient oral health status using the BOAS, CPOT, and patient self-report of oral health symptom intensity on randomly selected dates. We will provide each cluster lead with written feedback on these observations for dissemination to frontline ICU staff. For sites identified as having low intervention fidelity during audits (< 70% compliance across all bundle components), we will provide additional education and intensified audit frequency. We estimate observing a minimum of 25 patients in each ICU during the intervention phase (150 total).

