### Randomization and allocation concealment

Randomization of ICUs to the six sequential steps will be computer-generated by the study statistician. Each ICU will be randomly allocated to start the study intervention according to the randomized staggered implementation schedule and the sequence will be concealed until interventions are assigned. Clusters agreed to participate with the understanding that order of allocation to the intervention would be unknown in advance of randomization. Within control and intervention periods, random dates of observation at each site will be computer generated to collect oral health dysfunction scores and establish intervention fidelity in a subset of patients.

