#### Pre-and post-intervention oral care fidelity

In the 2 months preceding chlorhexidine de-adoption and implementation of a standardized oral care bundle, and then each month following implementation, trained study team members will collect oral care fidelity data using a structured observational tool on randomized dates. We will observe a minimum of 25 patients per ICU at pre-intervention and intervention phases for a total of 150 patients in each time period. We will report oral care fidelity as medians and IQR and analyze using the Wilcoxon rank sum test to compare the pre-intervention and intervention groups.

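### Audits intensified at ICUs with low fidelity can change the ICU mix of the intervention-phase sample, and the unstratified rank tests of fidelity, pain and symptoms would pass that change on

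*Protocol article*

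**What the plan says.** Under Randomization and allocation concealment, the protocol article states that "random dates of observation at each site will be computer generated to collect oral health dysfunction scores and establish intervention fidelity". One set of dates therefore serves both purposes.

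Under Intervention phase, starting one month after allocation, "a trained assessor will begin to observe fidelity of delivery of the oral care protocol and assess patient oral health status using the BOAS", together with CPOT and patient self-report. The sentences that follow link these observations to auditing. First, "We will provide each cluster lead with written feedback on these observations". Then, "For sites identified as having low intervention fidelity during audits (< 70% compliance across all bundle components"), the response is that "we will provide additional education and intensified audit frequency". The size of the increase is not given.

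On numbers, the section Pre-and post-intervention oral care fidelity says: "We will observe a minimum of 25 patients per ICU at pre-intervention and intervention phases for a total of 150 patients in each time period". The sections on the pre-intervention and intervention phases give the same floor. None gives a ceiling, and the pre-intervention section has no compliance trigger.

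On analysis, fidelity (Pre-and post-intervention oral care fidelity) and CPOT and self-reported pain and dryness (Statistical analysis) are summarized as medians and compared between phases by the Wilcoxon rank sum test, with no site term. BOAS is summarized as a mean and analyzed by a linear mixed model that accounts for site.

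**The concern.** The number of observations that an ICU contributes can depend on its own measured fidelity, and this can happen in one phase only. The control sample is planned at about 25 per ICU. The intervention sample may hold 25 from most ICUs and considerably more from any ICU that fell below 70%. Those extra observations also come after additional education.

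A two-sample rank test that ignores site treats a change in ICU mix as a change in outcome. At stake are the CPOT and symptom comparisons, and the fidelity comparison on which the process evaluation relies to interpret the trial result. Whether a visit was triggered is a fact of data collection. No later analysis can use it unless it was recorded or can be reconstructed.

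**Working it through.** **The plan's own figures.** 6 ICUs × 25 = 150 per phase, as stated. For BOAS, take SD 2, a difference of 2, the upper stated design effect of 10, and two-sided alpha 0.05 (assumed, because none is stated). Effective n = 150/10 = 15 per phase, SE = 2 × √(2/15) = 0.730, and power = Φ(2/0.730 − 1.96) = 78%, close to the stated 80%. The equal-sampling baseline is therefore coherent.

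**Share of observations from triggered ICUs.** The audit increase f is not stated, so f = 1.5 to 3 is assumed. With k triggered ICUs, share = 25fk / [25(6 − k) + 25fk].

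| Triggered ICUs | f = 1 | f = 1.5 | f = 2 | f = 3 |
|---|---|---|---|---|
| 1 | 25/150 = 16.7% | 37.5/162.5 = 23.1% | 50/175 = 28.6% | 75/200 = 37.5% |
| 2 | 50/150 = 33.3% | 75/175 = 42.9% | 100/200 = 50.0% | 150/250 = 60.0% |

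The control-phase share stays at 16.7% or 33.3%. If nothing changes within any ICU, the spurious difference in means between phases is (intervention share − control share) × site difference. For one triggered ICU and a site difference of 1 SD, that is 0.12 SD at f = 2 and 0.21 SD at f = 3.

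**Effect on the Wilcoxon test.** Simulation with 2,000 runs per scenario: normal outcomes with within-site SD 1, 25 per ICU in control, triggered ICUs differing from the rest by a stable 0.5 or 1 SD in both phases, and no within-site change. Proportion with p < 0.05:

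| Triggered ICUs | Site difference | f = 1 | f = 2 | f = 3 |
|---|---|---|---|---|
| 1 | 0.5 SD | 4.8% | 8.6% | 14.7% |
| 1 | 1 SD | 3.5% | 14.1% | 39.5% |
| 2 | 0.5 SD | 4.3% | 10.7% | 23.9% |
| 2 | 1 SD | 3.7% | 24.2% | 66.0% |

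**Effect on the BOAS mixed model.** A random-intercept model weights within-site contrasts approximately by n₀n₁/(n₀ + n₁). With n₀ = 25, the weight is 12.5 for n₁ = 25, 16.7 for n₁ = 50 and 18.75 for n₁ = 75. Assume an effect of −1 in triggered ICUs and −2 elsewhere.
- One triggered ICU: −1.83 (f = 1); (16.7 × −1 + 62.5 × −2)/79.2 = −1.79 (f = 2); (18.75 × −1 + 62.5 × −2)/81.25 = −1.77 (f = 3).
- Two triggered ICUs: −1.67, −1.60 and −1.57.
- One triggered ICU whose effect is −3 after re-education: −2.17, −2.21 and −2.23. The shift reverses.

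The largest shift is 0.10 point (−1.67 to −1.57), about 5% of the two-point target.

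**The case against.** The strongest reply is that the protocol article nowhere says the intensified audits record BOAS, CPOT or symptoms, or that they enter the outcome comparisons. It ties outcome observations to computer-generated random dates and plans 150 per phase, so an analysis set limited to those dates may be what was intended. This stands in part. Pooling is an inference, and enrichment also needs at least one ICU below 70%. But no separate audit stream is described, the word audits follows directly on the outcome observations, and nothing excludes the extra visits.

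Four stronger readings are tempting and are not supported:

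- **A reader might conclude that the BOAS effect is materially biased.** If BOAS is assumed to be 8 in five ICUs and 10 in one, the raw pooled mean moves from 8.33 to 8.57 (f = 2) or 8.75 (f = 3), which is 12-21% of the two-point target. That is a descriptive mean. The planned mixed model largely removes stable site differences.
- **A reader might expect reported fidelity to fall.** With 60% assumed in one low ICU and 85% elsewhere, mean fidelity goes from 80.8% to 77.9% or 75.6%. The plan reports a median, which in this example, with no within-ICU spread, stays at 85%. The exposure lies in the rank test and depends on the spread.
- **A reader might say the extra visits do not represent the care that most intervention patients in that ICU received.** The design gives 12 intervention months to the first ICU and 2 to the last. In early-step ICUs, re-education after an early audit would precede most intervention patients. Feedback and re-education are also part of the planned delivery.
- **A reader might infer a direction of bias.** Low performance and re-education pull opposite ways, so none is established.

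It is also fair to say that fidelity, CPOT and symptoms are not among the listed primary and secondary outcomes, and that handling of the analysis set could sit in an analysis plan that is not shown. The trigger and the unstratified rank tests are nevertheless stated choices in this document, and it is their combination that creates the exposure.

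**Conclusion.** The point holds in conditional form. If at least one ICU falls below 70% and its extra observations are pooled, the fidelity, CPOT and symptom comparisons can reject falsely because of ICU mix alone. The rate is roughly 9-39% with one triggered ICU and 11-66% with two, against about 5% or slightly less under equal sampling.

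These figures rest on an assumed two- to threefold increase in observations, stable site differences of 0.5 to 1 SD, normal outcomes and no within-site change. The document gives none of these quantities, and CPOT is a 0-8 score, so the figures show the order of size and are not predictions.

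BOAS inference is little affected (about 0.1 point or less in the scenarios run). ICU mortality and IVAC come from the iCORE registry and do not depend on audit sampling. The issue is worth correcting for the process evaluation and symptom results, but it does not threaten the primary analysis.

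**What to change.** Flag each triggered audit visit when it is scheduled and use its data for feedback only. Base the fidelity, CPOT, symptom and BOAS comparisons on the visits from the computer-generated random-date schedule. Scheduled visits that happen to follow re-education stay in.

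Where numbers per ICU still differ between phases, stratify the rank tests by ICU (for example, a van Elteren test). This could be needed even without the trigger, because fidelity is observed monthly after implementation and the ICUs have between 2 and 12 intervention months. Stratification deals with the ICU mix. Only the restriction to scheduled visits also removes the extra weight on post-re-education observations within an ICU.

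The article gives 31 March 2019 as the end of the trial. If visits were not flagged at the time, scheduled ones can still be identified from the generated list of dates, provided it was kept.

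The cost is one field on the visit form and a sentence defining the outcome dataset. The small downside is that triggered-audit data do not add to the outcome sample.

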### Outcome measures

The primary outcome is ICU mortality measured at the level of the patient. Secondary outcomes include: (1) IVAC rates; (2) and oral care dysfunction (BOAS) scores measured at the patient level.

### Data collection

iCORE is a local clinical registry that collects de-identified patient demographic and clinical data, including severity of illness, antibiotic usage, IVAC rates, and patient outcomes. We will use the iCORE registry to collect patient demographic and treatment characteristics (i.e., age, sex, co-morbidity, admission diagnosis, nature of admission (elective or emergent), and severity of illness (APACHE III score), as well as to determine outcome data including IVAC rates and ICU mortality. The BOAS tool [25], oral care delivery compliance, pain, and other oral symptoms will be prospectively measured by the investigator team.

### Sample size

#### Mortality

Recent systematic reviews [30] show that chlorhexidine increased mortality with an odds ratio (OR) of 1.25 (95% confidence interval (CI) 1.05–1.50). This corresponds to a risk ratio of 1.18 (95% CI 1.04–1.33) and an absolute reduction in mortality of 5% (95% CI 1%–6%). Six clusters averaging 50 ventilated patients per month for 14 months for a total of 4200 patients, assuming an intracluster correlation (ICC) of 0.001, provides about 80% power to detect an absolute reduction in mortality of 5.5% from a baseline rate of 26% [6, 31, 32].

#### Oral health dysfunction

The BOAS scale ranges from 5 to 20, with a score of 5 equivalent to no oral problems and 20 equivalent to the worst possible oral health state. Previous ICU studies report a mean (standard deviation) score of 10 (2) [26]. Taking into account clustering (DEF = 1 + (n − 1) × ICC with an ICC = 0.05 to 0.2), the design effect would range from 3.5 to 10 and therefore the sample size ranges from 86 to 300. We will observe a minimum of 25 patients per ICU at control and intervention phases. With 150 patients in each time period we have 80% power to detect a two-point decrease in the BOAS in the intervention group.

### Analysis and evaluation

#### Statistical analysis

We will describe our patient cohort and treatment characteristics using means and standard deviations or medians and interquartile ranges dependent on data distribution for continuous variables and frequencies and percentages for categorical variables. To account for clustering of patients within sites, the primary outcome, mortality, will be analyzed using a generalized linear mixed model (with logit link and binary distribution) adjusting for time to account for secular trends as well as important prognostic factors such as age, sex, APACHE III score, and comorbidities. We will inspect missing data and if less than 5% are missing we will use imputation by the median values for the continuous variables and mode for the categorical ones. If more than 5% of the sample has missing values we will use multiple imputations. Differences between the control and intervention periods and time trends will be estimated using OR and their 95% CIs. IVAC counts with offset number of ventilator days per patient will be analyzed using a generalized linear mixed model with log link and Poisson or negative binomial distribution as dictated by the distribution of the data. For mortality and IVAC rates we will exclude those patients who start in the control group and cross-over to the intervention group. BOAS will be summarized using mean and standard deviation and analyzed using linear mixed models (adjusting for clustering of patients within sites) with treatment phase as an independent variable. We will report the CPOT (oral pain during care delivery) scores, and patient self-report (pain, dryness) outcomes, as medians and IQR and analyze using the Wilcoxon rank sum test to compare the pre-intervention and intervention groups.

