## Methods/design

### Design

The CHORAL study is a SW-CRT. Each cluster (defined as a single ICU) will be randomly allocated to receive the intervention according to a staggered implementation schedule in one of six sequential steps comprising 2-month intervals. There will be six clusters in total with all clusters commencing with a 2-month control period (baseline) in which standard of care includes chlorhexidine oral care for IVAC prevention. Each cluster will maintain chlorhexidine oral care until they are allocated to crossover from control to intervention according to the randomization schedule. The study completes with a 2-month period during which all clusters have fully de-adopted chlorhexidine and implemented the standardized oral care bundle. Total study duration will be 14 months (Fig. 1). We follow CONSORT cluster trial extension guidelines for SW-RCTs in the design of this study [21]. The SPIRIT checklist is provided in Additional file 2.

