#### Patient inclusion criteria for SW-CRT

All adult patients who receive invasive mechanical ventilation in the participating ICUs and are able to receive standardized oral care can be included. For mortality and IVAC rates we will exclude those patients who start in the control group and cross-over to the intervention group.

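### Excluding control patients who are still under care in the ICU at crossover makes inclusion depend on a post-admission event in one condition only, with a bias of unknown direction

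*Protocol article*

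**What the plan says.** The primary outcome is fixed in Outcome measures: "The primary outcome is ICU mortality measured at the level of the patient". Under Patient inclusion criteria for SW-CRT the protocol says that, for mortality and IVAC rates, "we will exclude those patients who start in the control group and cross-over to the intervention group", and the Statistical analysis section repeats the rule: "For mortality and IVAC rates we will exclude those patients who start in the control group and cross-over to the intervention group". The article describes no analysis by phase at admission and no transition window based on dates.

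The Design section places each ICU "in one of six sequential steps comprising 2-month intervals", after a common 2-month baseline, and adds: "Total study duration will be 14 months". Crossover runs one way, from control to intervention. The sample size counts every ventilated patient, with no allowance for exclusions: "Six clusters averaging 50 ventilated patients per month for 14 months for a total of 4200 patients", "assuming an intracluster correlation (ICC) of 0.001".

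**The concern.** Take two identical patients admitted to the same ICU a week before its crossover. One dies or is discharged the day before crossover and stays in the control data. The other is alive in the unit on the day and is deleted, whatever happens next. Inclusion thus depends on what happened after admission, and what happened is bound up with the outcome. No intervention patient faces such a rule.

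Randomising the order makes the crossover date independent of prognosis, but not the set of patients still present on that date. Adjustment for time, age, sex, APACHE III and comorbidities does not help either, because selection acts on length of stay after admission.

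For mortality, control risk in the period next to each crossover is overstated or understated, depending on whether the deleted patients die less or more often than the rest. For IVAC, the outcome is a rate per ventilator day, so deleting long stays biases it if risk varies with time on the ventilator or if an IVAC prolongs ventilation. The Background section says that IVACs do prolong it, so by the protocol's own account control patients with an IVAC are more likely to be present at crossover and deleted.

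**Working it through.** **Inputs from the protocol.** 6 ICUs; a baseline plus six 2-month steps, so 7 periods; 50 patients a month, so 100 per ICU-period; 21 control and 21 intervention ICU-periods (2,100 patients each, 4,200 in all); ICC 0.001; mortality 26% falling to 20.5%.

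**Assumed.** Two-sided 5% level; mean ICU stay of 5, 10 or 15 days; mortality of the excluded patients 20% or 35%; 30.44 days per month.

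**1. The plan's power.** Stepped-wedge variance (Hussey-Hughes) with pooled risk (26 + 20.5)/2 = 23.25% gives SE = 1.93 points. Power = Φ(5.5/1.93 - 1.96) = 81.5%; with the control variance it is 78.5%. The stated figure of about 80% reproduces, so this model is a fair frame for the bias.

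**2. Weight on the affected cells.** The generalised least squares estimate is a weighted sum of the 42 cell means, with control weights summing to -1. The six last control cells together carry -0.52 (-0.69 if the ICC were 0.01). The share is uneven: from -0.03 for the first ICU to cross to -0.14 for the last.

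**3. Patients removed.** Number present at crossover n = (50/30.44) × mean stay = 8.2, 16.4 or 24.6 per ICU. Over six ICUs this is 49, 99 or 148, or 2% to 7% of 2,100 control patients, but 8% to 25% of each last control cell.

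**4. Shift and bias.** With excluded-patient mortality q, mortality in the depleted cell is m = (26 - n·q)/(100 - n). Bias = w × (m - 26%), with w recomputed for the smaller cells. Negative values flatter the intervention.

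| Mean stay | n per ICU | w | m, q = 20% | Bias | m, q = 35% | Bias |
|---|---|---|---|---|---|---|
| 5 days | 8.2 | -0.495 | 26.54% | -0.27 | 25.19% | +0.40 |
| 10 days | 16.4 | -0.468 | 27.18% | -0.55 | 24.23% | +0.83 |
| 15 days | 24.6 | -0.438 | 27.96% | -0.86 | 23.06% | +1.29 |

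At ICC 0.01 the 10-day row becomes -0.73 and +1.10. With an SE near 2.0, the 10-day biases are about 0.3 to 0.4 SE and raise the two-sided type I error from 5% to about 5.9% to 7.0%.

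**5. What sets the sign.** If patients who die stay Ld days on average and those who leave alive stay Ls, then q = 0.26·Ld/(0.26·Ld + 0.74·Ls). Under no true effect:
- Ld = Ls: q = 26%, bias 0.
- 6 and 10 days: q = 1.56/8.96 = 17%, bias -0.7.
- 12 and 8 days: q = 3.12/9.04 = 35%, bias +0.7.
- 5 and 15 days (extreme): q = 1.3/12.4 = 10%, bias -1.8, type I error 14.7%.

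**6. Cost of keeping everyone.** If crossing patients took on the full 5.5-point effect, dilution = 0.5205 × n/100 × 5.5 = 0.24, 0.47 or 0.71 points for 5, 10 or 15 days (up to 0.93 at ICC 0.01). Power = Φ((5.5 - dilution)/1.93 - 1.96) = 78%, 74% or 70%. The separate-stay scenarios (5 and 15, 6 and 10, 8 and 8, 12 and 8 days) give estimates of -4.9 to -5.3 points and power of 73% to 78%.

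**7. Cost of a date window.** Dropping all admissions in the 14 days before each crossover loses about 6 × 14 × 50/30.4 = 138 patients; SE = 1.99 and power = 79%. A one-month window loses 300 and leaves 75%.

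**The case against.** The rule has a sensible purpose: a patient treated under both conditions has mixed exposure, and leaving such patients out looks clean. Keeping them is not free. If they took on the full effect, the dilution (0.47 points at a 10-day stay) would be close to the selection bias it replaces (0.55 to 0.83). That stands, and it is why a date-based window deserves equal standing as the primary analysis. Dilution does differ in kind, however: it runs toward the null and vanishes when there is no effect, whereas the selection bias can run either way and is present under the null.

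It also stands that the size rests on assumed inputs, and that the census may be too high. The bundle and the de-adoption concern invasively ventilated patients, so someone extubated before crossover but still in the unit arguably does not cross over. If time on the ventilator sets the count, fewer patients are removed and the bias is smaller.

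A reader might infer that the rule strips survivors from the control group and so favours the intervention. The documents do not support that. Patients are removed for being alive in the unit on one date; some of them die later, and the sign depends on stays that the protocol does not report.

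**Conclusion.** The rule is wrong as written. It is stated twice, governs the primary outcome, and selects on a post-admission event in the control condition only; nothing else in the article offsets it. At the protocol's ICC, and with the assumed stays of 5 to 15 days and excluded-patient mortality of 20% or 35%, the mortality bias is between -0.86 and +1.29 points, and under 1 point in five of the six cases. That is moderate against a 5.5-point target, but it could help create or mask a signal, and the direction cannot be known from the documents. The IVAC bias cannot be sized from them.

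A reader might go further and take the trial's type I error to be badly inflated. The 14.7% figure needs survivors to stay three times as long as patients who die, and nothing in the documents shows that.

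**What to change.** Delete the exclusion in both Patient inclusion criteria for SW-CRT and Statistical analysis, and define inclusion for mortality by the date of ICU admission (or start of ventilation) alone. Two versions are acceptable:

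- (a) Keep every patient, classified by the ICU's condition on that date.
- (b) Drop everyone admitted within a fixed window before crossover, whatever their stay or outcome.

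Name one as primary and the other as the sensitivity analysis. For IVAC, keep crossing patients and censor their ventilator days and events at the crossover date.

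The change is a rewording of two sections, using dates that the registry should already hold. The statistical cost of (a) is the worst-case dilution and power loss in step 6; that of (b) is the loss of about 138 patients with a 14-day window. Under (b), patients admitted before the window who stay beyond crossover remain in control with mixed exposure, so the window length should be justified from registry data on stay.

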### Pre-intervention phase

#### Oral care observations

In the 2 months preceding de-adoption of chlorhexidine and introduction of a standardized oral care bundle at each site, a trained standardized assessor will use structured observational tools to document baseline oral care delivery, including chlorhexidine concentration and application method [23]. We will document pain presence (yes/no) during oral care using the Critical-Care Pain Observation Tool (CPOT; range 0–8, score > 2 indicating pain) [24], and oral health dysfunction using the Beck Oral Assessment Scale (BOAS) [25] on randomly selected dates. The CPOT was recently validated for detecting pain presence in non-verbal ICU patients during oral care delivery and the BOAS tool has been previously validated in the ICU population [26]. For patients able to self-report (mouth words, nod, point), we will also measure symptom intensity using a 0–10 intensity-rating scale for (i) oropharyngeal dryness and (ii) procedural oral pain [27] immediately following the oral care delivery. We aim to observe a minimum of 25 patients in each ICU during this baseline phase (150 total).

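### The stated BOAS model has treatment phase and site but no calendar time, so part of any secular drift would enter the estimated intervention effect

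*Protocol article*

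**What the plan says.** The Statistical analysis section of the protocol article describes three models in one paragraph.

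- **Mortality (primary):** a logistic mixed model, "adjusting for time to account for secular trends as well as important prognostic factors such as age, sex, APACHE III score, and comorbidities".
- **IVAC:** "IVAC counts with offset number of ventilator days per patient will be analyzed using a generalized linear mixed model with log link", with a Poisson or negative binomial distribution. The sentence gives the model family and the offset and lists no covariates.
- **BOAS:** "analyzed using linear mixed models (adjusting for clustering of patients within sites) with treatment phase as an independent variable". The clustering adjustment and an independent variable are both named, and time is not among them.

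The paragraph also says "Differences between the control and intervention periods and time trends will be estimated using OR and their 95% CIs". An odds ratio belongs to the logistic mortality model, so this sentence does not bring time into a model for a BOAS mean.

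On timing, ICUs cross over "in one of six sequential steps comprising 2-month intervals", and "Total study duration will be 14 months". Control BOAS observations are made "In the 2 months preceding de-adoption of chlorhexidine and introduction of a standardized oral care bundle at each site". Under Intervention phase, intervention BOAS observations begin one month after allocation, and no end of that window is given. The process-evaluation section on oral care fidelity has monthly data collection after implementation. Because BOAS is assessed alongside fidelity, this leans towards the longer window but does not settle it.

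**The concern.** In a stepped wedge, control data come on average earlier than intervention data, so phase and calendar time are correlated by design. A site effect does not remove this, because within each ICU all control observations precede all intervention observations. The six staggered crossovers allow time to be separated from treatment, but only if time is in the model. The protocol applies this reasoning to mortality and, in the same paragraph, does not carry it over to BOAS.

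BOAS is one of two named secondary outcomes, and better oral health is one of the trial's stated aims. A drift in case mix, staffing or general nursing practice over 14 months would be partly credited to the bundle. A drift in the other direction would partly hide a real effect.

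**Working it through.** **The plan's own figure.** Sample size, Oral health dysfunction: SD 2, difference 2 points, 150 patients per phase, design effect 3.5 to 10, power 80%. Two-sided 5% is assumed, since the article does not state it. At a design effect of 10 the effective size is 150/10 = 15 per phase. Then z = 2 / (2 × √(2/15)) = 2.74, and power = Φ(2.74 − 1.96) = 0.78. The stated 80% is reproduced to within two points at the upper design effect. At 3.5 the power is 0.996.

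**Calendar position of the observations.** ICU k (k = 1 to 6) crosses over at month 2k. Observations are assumed evenly spread within each window.

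| Window | Midpoint for ICU k | Mean over six ICUs |
|---|---|---|
| Control, months 2k−2 to 2k | 2k − 1 | 6.0 |
| Intervention, short: months 2k+1 to 2k+2 | 2k + 1.5 | 8.5 |
| Intervention, long: months 2k+1 to 14 | k + 7.5 | 11.0 |

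The gap is 8.5 − 6.0 = 2.5 months or 11.0 − 6.0 = 5.0 months. With 25 patients before and 25 after in every ICU, the phase coefficient of the model without time absorbs exactly this gap, whatever the ICC. As a share of 14 months: 2.5/14 = 18% and 5.0/14 = 36%.

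**Standard error without time.** With a random ICU intercept and each ICU as its own control, SE = 2 × √((1 − ICC) × 2/150). For the protocol's ICC range of 0.05 to 0.2 this gives 0.225 to 0.207.

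**Spurious effect and false-positive rate.** Bias = gap × monthly drift. False-positive rate = Φ(−1.96 − bias/SE) + 1 − Φ(1.96 − bias/SE). The drift rates are assumptions.

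| Assumed drift (points/month) | Window | Bias (points) | False-positive rate (ICC 0.05 to 0.2) |
|---|---|---|---|
| 0.05 | short | 0.125 | about 9% |
| 0.05 | long | 0.25 | 20% to 23% |
| 0.1 | short | 0.25 | 20% to 23% |
| 0.1 | long | 0.5 | 60% to 68% |

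**With time in the model** (generalised least squares, random ICU intercept, same observation pattern). A linear month term leaves no bias from linear drift. Two-month period indicators leave about 0.3 to 0.5 month of drift, because observations are ordered within a period. At 0.1 points a month that is at most 0.05 points, and the false-positive rate stays near 5%. The SE becomes 0.27 to 0.35. At 0.352, power for two points is Φ(2/0.352 − 1.96) > 0.99.

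**Why this exceeds the protocol's 80%.** The protocol's design effect treats the two phases as separate sets of clusters. Here each ICU contributes to both phases, so a shared intercept cancels. The figure above 99% allows for neither ICU-by-period variation nor a small-sample correction for six ICUs. The documents give no value for the former, so the figure is optimistic.

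**The case against.** **The BOAS sentence calls phase an independent variable, not the only one, and a separate analysis plan might add time.** This is fair as a matter of wording. But the article does state a BOAS model, names its clustering adjustment and its predictor, and puts time adjustment explicitly in the mortality sentence beside it. A reader following the article would fit the model without time. An unseen plan does not correct a stated model.

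**The drift is hypothetical.** This stands. No BOAS trend appears in the documents. At 0.1 points a month the drift over the trial would be 1.4 points, or 0.7 SD, which is large. The 68% needs that drift, the long window and the upper ICC together. Only the 2.5 to 5.0 months absorbed follow from the schedule, given linear drift and even spacing.

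**Staggering already removes much of the trend.** This also stands. The absorbed share is 18-36%, so it would be wrong to say that the whole of a secular trend is counted as intervention effect. Seasonality depends on the window too: an annual sine wave cancels exactly with the short window but not with the long one (up to 0.45 of its amplitude remains).

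**Education and feedback are not secular drift.** This is correct. Education precedes each ICU's own crossover and written feedback follows it. Both are part of delivering the intervention, and a calendar term neither would nor should remove them.

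**IVAC.** A reader might infer that the IVAC model has the same fault, so that both secondary outcomes are exposed. The text does not support that. The IVAC sentence names no treatment term either, so it cannot be a full covariate list. It is silent on time, and a condensed article may leave that to the full plan.

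**Conclusion.** The point holds for BOAS. The stated model omits calendar time in a design where phase and time are confounded, and the phase estimate would carry 2.5 to 5.0 months of any linear drift. How much that matters depends on an unknown trend. Under the assumed 0.05 to 0.1 points a month (SD 2, 150 per phase, ICC 0.05 to 0.2, two-sided 5%, random intercept only), the bias is 0.13 to 0.5 points.

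A reader might infer that drift alone could produce the effect the trial looks for. It could not at these rates: 0.5 points is 25% of the planned two-point difference. What is at risk is the validity of the test and the accuracy of the estimate. The primary outcome is adjusted for time and is unaffected. This is a should-fix point confined to one secondary outcome.

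**What to change.** Add calendar time to the BOAS linear mixed model, for example: BOAS will be analysed with a linear mixed model containing treatment phase and calendar time as fixed effects and ICU as a random effect.

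The form of time should be fixed in advance. Linear month removes linear drift fully but not a curved or seasonal pattern. Two-month period indicators handle such patterns better but leave the small within-period residual shown above. The end of the intervention observation window should be stated as well, since it sets the size of the confounding.

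The cost is one sentence and some precision: SE from about 0.21-0.23 to 0.27-0.35 under a random-intercept model, with power for two points still high. No further patients or data items are needed beyond the observation date. For IVAC, simply confirm that the same time term is included.
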